## Abstract

**Background:**

Impaired glucose tolerance (IGT) is associated with being overweight/obesity and is a powerful risk factor for the disease of diabetes. In addition to lifestyle intervention that shows limited clinical application, acupuncture treatment has been a feasible treatment method for IGT in clinical practice. However, the effectiveness of acupuncture treatment has not been proved in evidence-based practice. Therefore, we design a multicenter randomized controlled trial to evaluate the efficacy and safety of acupuncture treatment for IGT in people with overweight/obesity.

**Methods:**

The trial will be conducted at hospitals in three different sites in China. A total of 196 participants will be recruited and randomly assigned at a ratio of 1:1 to either to the acupuncture group or the sham acupuncture (SA) group. Both groups will receive 30 sessions of treatment for 12 consecutive weeks and will be provided with lifestyle intervention and a 24-week follow-up. The primary outcome will be change in the baseline value of 2-h blood glucose (2hPG) on the 12th week. Additionally, the expectancy of acupuncture, blinding, and safety will also be assessed. All statistical analyses will be performed by two-sided test, and a *p*-value of less than 0.05 will be considered statically significant.

**Discussion:**

This study aims to provide quantitative clinical evidence of acupuncture effectiveness and safety in treating IGT in people who are overweight/obese.

**Clinical Trial Registration:**

[www.ClinicalTrials.gov], identifier [NCT05347030].

## Introduction

Impaired glucose tolerance (IGT), measured by oral glucose tolerance test (OGTT), is an intermediate stage of hyperglycemia between normoglycemia and diabetes (1, 2). The latest research shows that 541 million adults, or 10.6% of adults worldwide, are suffering from IGT (3), with China as the top epicenter. Owing to the similar pathophysiological mechanism of insulin resistance (4–6), IGT is more commonly seen in people who are overweight/obese. The prevalence of IGT in people who are overweight/obese in China reached 46.6% in 2008 (7). If no intervention is administered, every year, about 7% of individuals with IGT will develop diabetes (8), which is deeply associated with many chronic and acute diseases (3, 9, 10). Meanwhile, vascular complications associated with type 2 diabetes mellitus (T2DM) could occur in the IGT stage, indicating increased risks of cardiovascular and cerebrovascular diseases, microvascular diseases, tumors, and dementia in the future (11–15). Additionally, both pre-diabetes (including IGT) and obesity, like diabetes, have been determined as risk factors for critical coronavirus disease 2019 (COVID-19) (16–18). These diseases tend to cause a great damage to organs, warrant long-term interventions, and require large costs, posing a great challenge to public health across the globe (19).

Fortunately, the hyperglycemia in IGT is reversible (20), which means it is possible to prevent or delay the development of diabetes. At present, the recognized effective interventions include lifestyle modifications and pharmaceuticals.

Lifestyle modifications, including a healthy diet and more physical activity, are first-line treatments for patients with IGT who are overweight/obese (21–24). Research studies in different geographical areas globally have shown that lifestyle modifications reduce the risk of diabetes by more than 50% (8, 25, 26). However, it is difficult to apply the method concluded from lifestyle trials into clinical practice considering the high cost, considerable resources required, and lack of participant adherence to the intervention (27, 28). According to the Finnish Diabetes Prevention Study Group’s study, only 47% of the intervention group had a dietary fat intake of less than 30%, only 36% increased exercise intensity, and only 43% reached the weight loss target (26). Besides, patients with other diseases such as ischemic heart disease are excluded from this benefit, because their physical condition prevents them from achieving the recommended intensity of physical activity.

Several pharmaceuticals have been applied in treating IGT. Metformin was the first medicine shown to be effective (25), and it is also the only drug recommended by the American Diabetes Association for IGT treatment. However, Metformin is less effective than lifestyle modifications (31% vs. 58%), has adverse effects such as gastrointestinal reactions, and is not advised for all subgroups (25). The United States Food and Drug Administration has not approved it for preventive interventions (21). Acarbose is the only available medicine in China for treating IGT. Studies have shown that the risk of patients with IGT developing diabetes within 3.3 years is reduced by 25% (29), but many patients cannot tolerate its gastrointestinal side effects, and the drug is relatively expensive (30). As no sufficient evidence has shown that medication carries long-term efficacy and health economic benefits, relevant guidelines do not widely recommend medication intervention as the major measure to treat IGT.

Therefore, it is urgent to find a treatment method that not only treats IGT in people who are overweight/obese but is also characterized by the advantages of high safety, high compliance, good tolerance, and cost-efficiency.

As an important Traditional, Complementary, and Integrative Medicine (TCIM) therapy, acupuncture treatment has been more and more adopted in clinical practice all over the world. Its efficacy and safety have been preliminarily demonstrated in the treatment of insulin resistance (IR)-related diseases such as obesity, diabetes and its related complications, polycystic ovary syndrome, and hypertension (31–36). Although the physiological and pathological mechanisms of IGT are also related to IR (37, 38), the potential role of acupuncture in the treatment of obese people with IGT has not yet been determined by a well-designed randomized controlled trial (RCT). Therefore, this study is conducted to evaluate the efficacy and safety of acupuncture versus sham acupuncture (SA) on improving glucose metabolism among IGT people with Overweight/Obesity.

## Methods and Analysis

### Study Design

This is a prospective, multicenter, parallel-group, participant- and assessor-blinded randomized trial comprising a comparison between acupuncture and SA treatment for IGT in obese or overweight participants. All procedures and time frames are displayed in Figure 1 as per the guideline CONSORT.

**FIGURE 1 F1:**
[figure not shown]
Flow chart. BMI, body mass index; WHR, waist-to-hip ratio; FPG, fasting plasma glucose; FINS, fasting serum insulin; HOMA-IR, homeostasis model assessment-insulin resistance index; TC, serum total cholesterol; TG, triglyceride; LDL-C, low-density lipoprotein cholesterol; HDL-C, high-density lipoprotein cholesterol; BP, blood pressure; IWQOL-Lite, Impact of Weight on Quality of Life-Lite Questionnaire; and SNAQ, Simplified Nutritional Appetite Questionnaire.

### Participants

A total of 196 participants with IGT who are overweight/obese will be recruited from three different hospitals, Guang’anmen Hospital, Shenzhen Luohu District Traditional Chinese Medicine Hospital, and Yan Tai Hospital of Traditional Chinese Medicine, through public advertisements like posters, hospital websites, WeChat public accounts, and the Internet from October 2022 to December 2024. The research staff will introduce the background and process of the study in detail to potential subjects who contact the research team and express interest to participate. Once the informed consent form is signed, participants will be evaluated for eligibility by medical history inquiries, physical examinations, and necessary chemical examinations. The duration of the study for each participant will be 37 weeks, including 1-week baseline period, a 12-week treatment period, and a 24-week follow-up period.

### Diagnosis Criteria

The trial will adopt the diagnostic criteria of the World Health Organization [WHO (39)] for IGT (40) and the diagnostic criteria for overweight/obesity in the guidelines for the Prevention and Control of overweight and Obesity in Chinese Adults formulated by the Ministry of Health of China in 2003 (41, 42):

(1)IGT: fasting blood glucose (PG) is lower than 7 mmol/L, and 2-h blood glucose (2hPG) after oral 75 g glucose tolerance test (OGTT) is between 7.8 and ∼11.1 mmol/L.(2)overweight: 24 < BMI ≤ 27.9, obesity: BMI ≥ 28, or BMI ≤ 24 but waist circumference ≥ 85 cm (men)/ ≥ 80 cm (women).

Note: The above two criteria should be met at the same time.

### Inclusion Criteria

Participants who meet all of the following criteria might be eligible: (1) those who meet the diagnostic criteria for overweight/obesity and IGT; (2) 18–60 years old; (3) those who can appropriately describe their wishes, voluntarily fill in the informed consent form, and agree to participate in clinical trials.

Note: The above three criteria should be met at the same time.

### Exclusion Criteria

Participants will be excluded if they meet any of the following criteria: (1) obesity secondary to heredity, drugs, and diseases; (2) those who have received weight-loss treatment or antidiabetic treatment including acupuncture, drugs, herbal medicine, and nutrient supplements in the past 3 months; (3) those who have taken drugs that have known effects on body weight or appetite in the past 3 months, such as corticosteroids, antidepressants, non-selective antihistamines *in vivo*, and nicotine substitutes; (4) IGT caused by abnormal thyroid function, endocrine tumors, or extensive liver damage; (5) abnormal glucose tolerance caused by thiazide diuretics, β-blockers, nicotinic acid drugs, quinolones, calcineurin inhibitors, interferon-alpha, etc.; (6) participants with serious primary diseases such as heart, lung, brain, liver, or hematopoietic system diseases, progressive malignant tumor, or other serious consumptive diseases; (7) participants with cognitive impairment and severe mental illness; (8) participants with blood coagulation dysfunction and who are scare of needles; (9) pregnant, breastfeeding, or planning to conceive within 37 weeks.

Note: Participants who meet any of the above criteria should be excluded.

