### Sham Acupuncture Group

Participants in the SA group will receive minimal acupuncture at sham acupoints, which are located at a horizontal distance of one B-cun (≈ 20 mm) to the points used in the acupuncture group.

For sham EX-B3, BL18, BL20, and BL21, needles will be vertically inserted at a depth of 1–2 mm without any manipulation to avoid de-qi sensation and will be withdrawn immediately afterward.

For sham GV20, GV29, LI11, CV12, CV10, ST25, CV6, CV4, ST40, and SP6, needles will be vertically inserted at a depth of 1–2 mm without any manipulation to avoid the de-qi sensation. The needles will be retained for 30 min during each treatment session.

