### Rescue Medication

The participants will not be encouraged to receive any other treatment or medication for IGT or obesity/overweight during the study period to avoid any influence on the results. If participants receive any other treatment, they will also be included in this study, but all details will be recorded in the case report form.

If diabetes is diagnosed during the study period and regular hypoglycemic drugs are recommended by the specialists, the participants will be allowed to use hypoglycemic drugs for rescue. The details (name, dosage, frequency, start time, and duration of use) of drugs will be documented. The proportion of participants using rescue drugs in the groups will be compared.

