### Blinding Assessment

Blinding will be assessed using the James and Bang blinding indices (53). The participants will be told that they are 50% likely to be allocated to the traditional acupuncture group with deeper needling or to the modern acupuncture group with shallower needling. After the last treatment on week 12, each participant will be assessed with a questionnaire asking, “do you receive traditional acupuncture?,” with choice options of Yes or No.

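### The acupuncture washout and the on-study treatment rule are limited by indication, so real acupuncture for other conditions is allowed and could dilute the sham comparison

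*Protocol article*

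**What the plan says.** Exclusion (2) removes "those who have received weight-loss treatment or antidiabetic treatment including acupuncture, drugs, herbal medicine, and nutrient supplements in the past 3 months". Acupuncture appears there as one form of weight-loss or antidiabetic treatment, and no other criterion mentions it. Exclusion (3) removes "those who have taken drugs that have known effects on body weight or appetite in the past 3 months"; it covers drugs only, but it selects them by what they do, not by why they were prescribed.

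During the study, the Rescue Medication section says: "The participants will not be encouraged to receive any other treatment or medication for IGT or obesity/overweight during the study period". It continues: "If participants receive any other treatment, they will also be included in this study, but all details will be recorded in the case report form". Table 1 has a row for concomitant drugs at every visit and no row for non-drug treatment.

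The control is minimal needling: "Participants in the SA group will receive minimal acupuncture at sham acupoints". The Introduction supports testing acupuncture in impaired glucose tolerance by citing preliminary efficacy in "insulin resistance (IR)-related diseases such as obesity, diabetes and its related complications, polycystic ovary syndrome, and hypertension".

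**The concern.** In a sham-controlled trial, the exposure most worth controlling outside the trial is the experimental treatment itself. Here both the entry rule and the on-study rule depend on the reason for needling. A person being needled for pain, hypertension or polycystic ovary syndrome fails no stated criterion on that account, and nothing discourages continuing through week 36. The Introduction lists the last two conditions among the insulin-resistance-related diseases that it uses to motivate the trial, so its reasoning does not let one assume that such needling leaves glucose unchanged.

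The treatment of drugs makes the gap stand out. A drug that affects weight or appetite excludes whatever its indication, while acupuncture excludes only for certain indications.

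At stake is dilution. Real acupuncture received by sham participants would shrink the difference in 2hPG change at week 12. The Discussion already names false-negative results from an active sham as a limitation, and this would be an avoidable addition.

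**Working it through.** **1. What the text permits.** Take a person receiving acupuncture for a condition other than weight or glucose.

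- Exclusion (2): not met, because the treatment is neither weight-loss nor antidiabetic.
- Exclusion (3): not met, because it covers drugs.
- Rescue Medication, first sentence: silent, because it covers treatment for impaired glucose tolerance or overweight/obesity.
- Rescue Medication, second sentence: the person stays in the study and details are recorded.

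So entry and continuation are both permitted in either arm.

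**2. Inputs for a bound.** From Sample Size Calculation: pilot change in 2hPG of -1.16 ± 0.42 (acupuncture) and 0.97 ± 0.34 (sham) mmol/L; 98 per group; 80% power; two-sided 0.05; 10% dropout. The printed difference is 0.97 + 1.16 = 2.13. If a minus sign was lost before 0.97, it is 1.16 - 0.97 = 0.19. Pooled SD = √((0.42² + 0.34²)/2) = 0.382. Completers = 98 × 0.9 ≈ 88 per arm. The share f of sham participants with outside acupuncture is not given; it is assumed.

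**3. The plan's own figure.** 98 per group does not follow from these inputs. With 2.13, the normal approximation gives 1 per group before dropout and 2 after. With 0.19, it gives 64 (65 by t-test), or 72 to 73 after dropout. The nearest match is 0.19 at 90% power: 86 by t-test, 96 after dropout, but the plan states 80%. This mismatch is a separate matter. It matters here only because the power figures below start near 91%, not 80%.

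**4. Dilution.** Suppose a share f of the sham arm gets the full acupuncture effect.

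- Difference: d = 0.19 × (1 - f)
- Sham variance: (1 - f) × 0.34² + f × 0.42² + f(1 - f) × 0.19²
- s = √((0.42² + sham variance)/2)
- Power = Φ(d / (s√(2/88)) - 1.96)

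For f = 10%: d = 0.171; sham variance = 0.1040 + 0.0176 + 0.0032 = 0.1249; s = √((0.1764 + 0.1249)/2) = 0.388; power = Φ(0.171/0.0585 - 1.96) = Φ(0.96) ≈ 83%.

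| f | d (mmol/L) | s | power |
|---|---|---|---|
| 0% | 0.190 | 0.382 | 91.0% |
| 5% | 0.1805 | 0.385 | 87.5% |
| 10% | 0.171 | 0.388 | 83.2% |
| 15% | 0.1615 | 0.391 | 78.2% |
| 20% | 0.152 | 0.394 | 72.6% |

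Power passes below 80% between 10% and 15%. With 2.13 in place of 0.19 throughout, power stays at about 100% up to f = 30%, the largest share tried, although the estimate still shrinks (at 10%, 2.13 × 0.9 = 1.92).

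**The case against.** The strongest reply is that this is a possibility with no evidence of its size. No section reports how often participants have acupuncture elsewhere or that it changes 2hPG. At least two of the three sites are traditional Chinese medicine hospitals by name, but recruitment is by public advertisement, and participants already attend 30 trial sessions. The Discussion ties the effect to specific acupoints with de qi, so needling at other points need not act on glucose. All of this stands, and it is why the power figures are a worst case at each assumed share: outside acupuncture for another complaint is credited with the whole effect of the trial regimen, in the sham arm only.

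It is also true that other treatment is to be recorded on the case report form, in a sentence with no indication limit on its face. That stands too. But the sentence follows one confined to impaired glucose tolerance and obesity, Table 1 schedules only drugs, and recording does not prevent dilution.

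The breadth of a washout is a design judgement, and a condensed article may leave operational detail to the full protocol. However, the article does print the rule, with its scope, and the point concerns that scope.

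A reader might infer two stronger claims. The first is that earlier acupuncture biases the comparison through the baseline. It does not: exposure before 1:1 randomization is balanced in expectation, and everyone must still meet the 2hPG entry range. The second is that a wider washout would restore blinding against people who know de qi. Participants are told they may enter the "traditional acupuncture group with deeper needling or to the modern acupuncture group with shallower needling", so shallow needling does not by itself reveal a sham. Someone last needled four months ago would also pass a 3-month washout with the same knowledge.

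**Conclusion.** The point holds as a gap in a stated rule: acupuncture for other indications is uncontrolled at entry and during the study, and in the sham arm it could dilute the effect towards the null. That crossover actually occurs, or is common, is not shown and should not be read into the documents.

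The loss is at most about 3, 8 or 18 percentage points of power at assumed shares of 5%, 10% or 20%. This rests on a difference of 0.19 mmol/L, the pilot SDs, 88 completers per arm and full effect from the outside treatment. If the printed 2.13 is right, power is not affected. The case for changing the wording rests on its low cost and on consistency with the effect-based drug exclusion, not on a demonstrated threat to the result.

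**What to change.** - Reword exclusion (2) so that acupuncture for any indication in the past 3 months excludes. Keep the indication limit for drugs, herbal medicine and supplements.
- Reconcile the first sentence of Rescue Medication with that scope, so that entry and on-study wording treat acupuncture in the same way.
- State that the existing case-report-form record of other treatment includes acupuncture outside the trial, with date and indication, and add it to Table 1 beside the drug row.
- Keep the intention-to-treat comparison as primary. Any analysis that accounts for outside acupuncture should be labeled supplementary, because it conditions on something that happens after randomization.

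The cost is one eligibility phrase, a matching edit in Rescue Medication and one form line. A few otherwise eligible recent acupuncture users will be turned away or wait 3 months.

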### Randomization and Allocation Concealment

A random number will be generated with the SPSS software and concealed in opaque random envelopes. The envelopes will be prepared by a third party in advance, with the sequence number labeled on the surface and the random number and group allocation information sealed in. The random envelopes will be preserved by special personnel who are not involved in treatment and evaluation.

### Blinding

The participants will be blinded to the group allocation in this study, while the acupuncturists will not be blinded. The outcome will be evaluated by independent assessors who will be blinded to the allocation to minimize the bias associated with data collection. The statisticians will also be blinded to the allocation.

### Intervention

Study group: acupuncture + lifestyle recommendation; control group: sham acupuncture + lifestyle recommendation.

During the 12-week treatment, participants in both the acupuncture and SA groups will receive 30-session treatment, three times per week (once every other day) in the first six weeks and twice per week (with an interval of 2–3 days) in the last six weeks. Certified acupuncturists with no less than one year of clinical experience will perform the treatment. Acupuncture needles (Huatuo, Suzhou Medical Appliance) with the size of 0.3 mm × 40-75 mm will be used in the acupuncture group, while, acupuncture needles (Huatuo, Suzhou Medical Appliance) with the size of 0.2 mm × 25-40 mm will be used in the SA group. The participants in different groups will be treated separately to avoid contamination during the process.

### Acupuncture Group

The acupuncture point regimen is based on evidence-based clinical practice guidelines of traditional Chinese medicine (43, 44). All acupoints selected and their locations are displayed in Figures 2, 3. For acupoints EX-B3 (Yishu), BL18 (Gansu), BL20 (Pishu), and BL21 (Weishu), needles will be inserted at a depth of 15–25 mm depending on the participants’ somatotype and at an angle of 20° obliquely downward. The needles will be gently rotated and lifted three times to achieve a sense of sourness, distention, and heaviness (*de qi*), and will be withdrawn afterward immediately.

**FIGURE 2 F2:**
[figure not shown]
Stimulation points of the acupuncture group and the sham acupuncture group (back view).

**FIGURE 3 F3:**
[figure not shown]
Stimulation points of the acupuncture group and the sham acupuncture group (front view).

For GV20 (Baihui), the needle will be inserted backward under the cap membrane at an angle of 45° with the scalp; for GV29 (Yintang), the needle will be inserted downward at an angle of 15° under the periosteum; making the participant feel heavy pressure and acid distension. For acupoints LI11 (Quchi), CV12 (Zhongwan), CV10 (Xiawan), ST25 (Tianshu), CV6 (Qihai), CV4 (Guanyuan), ST40 (Fenglong), and SP6 (Sanyinjiao), needles will be inserted at a depth of 25–35 mm vertically. The needles will be gently rotated and lifted three times to achieve a sense of sourness, distention, and heaviness (de qi). The needles will be retained for 30 min with gentle lifting, thrusting, and twirling every 10 min during each session.

Acupoint location refers to the standard of acupoint location in the western Pacific region of the WHO and the name and location of acupoints (GB/T12346-2006).

